#### Cost-effectiveness

Cost-effectiveness of treatment strategies is evaluated by incremental net-benefit analysis
[46]. Net health benefit addresses cost-effectiveness ratios by assuming values for the willingness to pay per unit of effectiveness. The cost analysis includes both medical (medication, visits, and hospitalizations) and non-medical costs (productivity losses, informal care). Other costs are estimated using quarterly cost questionnaires
[34] Costs are valued according to standard prices charges
[47] including time and travel costs.

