#### Endpoint evaluation

Patients in practices randomized to the MS strategy, and those patients in the IS and ES strategy not willing to participate in IBSM support, will only be approached for an endpoint evaluation at six months after their start with PatientCoach.

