**Costs**			
Healthcare and other costs (CostQ)	X	X	X, N

A = all strategies; X = Intermediate and Extended strategy; N = non-participating practices.

Asthma control is using the 7-item Asthma Control Questionnaire (ACQ), the optimal cut-point for ‘controlled’ is ≤0.75 and a value of ≥1.50 confirms ‘not controlled’ asthma
[28]. Lung function will be measured as the Forced Expiratory Volume in one second (FEV_1_). Patients receive a handheld electronic spirometer (PiKo-1: Ferraris; Hertford, UK) and are instructed to report the highest value of three measurements in the morning before taking medication
[1]. The presence of exacerbations is assessed; they are defined as deterioration in asthma that required emergency treatment or hospitalization (collected by quarterly questionnaire) or the need for oral steroids for three days or more (collected by pharmacy records) or the need for oral steroids for asthma as judged by the attending physician.

Exacerbations are defined according to ATS/ERS statement
[40]:

Severe exacerbations require at least one of the following: systemic corticosteroids (tablets, suspension, or injection) usage or an increase from a stable maintenance dose, for three or more days; or a hospitalization or emergency room visit because requiring systemic corticosteroids.

Moderate exacerbations require ≥ 1 of the following features, lasting for two or more days: deterioration in symptoms, deterioration in lung function, and/or increased rescue bronchodilator use.”

Health education impact is assessed by the health education impact questionnaire (heiQ)
[41]. Self-reported medication adherence is measured by the Medication Adherence Report Scale
[32]. Illness perceptions are assessed by using the Brief Illness Perception Questionnaire (Brief IPQ)
[33]. In addition, asthma symptom utilities are obtained from the Asthma Quality of Life Questionaire (AQLQ)
[42], EQ-5D
[31,43] and a visual analogue scale (VAS).

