#### Economic evaluation

The economic evaluation includes outcomes on cost-effectiveness and cost-utility. Medical costs, such as prescribed medication are assessed from electronic patient records (with written patient permission) complemented with the patient’s report on medication purchased elsewhere
[44]. In addition, actual treatment advice by the care provider and treatment advice by the system are registered. Healthcare consumption, absenteeism and productivity loss, and the number of limited activity days are measured by using the Cost Questionnaire
[34]. Furthermore, data on patient contacts (frequency of in-practice routine asthma consultations, telephone/email consultations, and unscheduled visits) are registered.

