#### Economic evaluation

The economic evaluation compares differences in societal costs to differences in the number of limited activity days (CEA) and quality-adjusted life years (CUA). The analysis has a six-month time horizon, without discounting. Group averages are statistically compared using two-sided bootstrapping and net-benefit analyses are used to compare costs to patient outcome. Sensitivity analyses are performed on the perspective (societal versus healthcare perspective) and the applied utility measure (Dutch EQ5D, VAS).

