## Discussion

This study is designed to investigate the effectiveness and cost effectiveness of implementing IBSM by comparing three different implementation strategies (MS, IS, and ES) in a three-arm cluster-randomized trial with a cluster pre-randomization design. The IBSM application contains functionalities that are characterized by some innovative aspects, such as options for e-consultation and integration of results into the general practice system. These functionalities address previously stated requirements for both patients and professionals. The findings of this study will lead to recommendations for a potential cost-effective strategy that can be used for the implementation of IBSM in practice.

This study has been designed for translation of research findings into actual practice. Primarily, the pre-cluster randomization design allows us to study the effect of the different implementation strategies on the number of primary care practices that participate in IBSM. Second, the impact of the different strategies at both professional and patient level on actual implementation (*i.e.*, participation, patient outcomes, and cost-effectiveness). Third, general practices are given a leading role to adapt and internalize IBSM in clinical practice: the project team will only act as facilitators to these practices. Additionally, the influence of research activities on implementation has been incorporated in the design of this study, because these might function as an extra stimulus for both practices and patients to adapt and internalize IBSM during the study period. Therefore, the content of the MS strategy is not only similar to commonly used (non-tailored) implementation strategies, but also the number and amount of research activities are minimized. This is in contrast to the IS and ES strategies, which are specifically designed to address previous identified barriers. These differences give us the opportunity to study how much support is required by general practices for IBSM implementation. Finally, this study evaluates the costs of the implementation from a societal perspective, which is in contrast to other implementation studies
[18,48]. Therefore, we will include costs for asthma care from both non-participating practices and non-participating patients.

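### The cost questionnaire is scheduled differently by strategy with no stated recall period, so questionnaire-based costs and limited activity days may be under-counted, most of all in the minimum strategy

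*Protocol article*

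**What the plan says.** All references are to the protocol article.

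- **Frequency of the form.** Cost-effectiveness: "Other costs are estimated using quarterly cost questionnaires".
- **Horizon.** Economic evaluation (under Analysis): "The analysis has a six-month time horizon, without discounting". Societal costs are set against limited activity days and QALYs.
- **Schedule.** In Table 4, the row that begins "Healthcare and other costs (CostQ" carries X at 0 and 3 months, and X and N at six months. The legend reads "A = all strategies; X = Intermediate and Extended strategy; N = non-participating practices".
- **Who is seen once.** The Endpoint evaluation section names two groups: "Patients in practices randomized to the MS strategy, and those patients in the IS and ES strategy not willing to participate in IBSM support". It says that both of these groups "will only be approached for an endpoint evaluation at six months after their start with PatientCoach". Study design likewise gives MS patients a six-month evaluation only.
- **Whose costs count.** Discussion: "we will include costs for asthma care from both non-participating practices and non-participating patients".
- **Other sources.** Economic evaluation (under Measurements and outcomes): "Medical costs, such as prescribed medication are assessed from electronic patient records (with written patient permission"). The same section says that contacts with the practice are registered. It assigns healthcare consumption, absenteeism, productivity loss and limited activity days to the CostQ.

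**The concern.** A form called quarterly and given once does not obviously fill a six-month horizon. IS and ES participants have forms at 3 and 6 months. MS patients and IS/ES decliners have at most one.

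If that single form looks back three months, their first quarter is missing for every item that only the CostQ supplies. The loss is tied to allocation. It affects everyone in MS but only the decliners in IS and ES, and participation is what the strategies are meant to change. MS would then show fewer limited activity days and lower questionnaire-based costs with no true difference. Both errors favour MS in the net-benefit analysis and work against the hypothesis that IS and ES are more cost-effective.

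**Working it through.** **1. The plan's own figures.** The article gives no captured share of costs to reproduce. Its one computed figure is the sample size. Taking 5% against 30% (an increase of 25 points), two-sided alpha 0.05, 80% power and a continuity correction gives 43 per arm. The design effect is 1 + 9 × 0.25 = 3.25. Then 43 × 3.25 = 139.75, so 140 per arm and 420 in total, as stated. This supports reading the increase as percentage points. The 30% is borrowed below for illustration only.

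**2. The CostQ schedule, passages side by side.**

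| Group | Table 4 | Study design / Endpoint evaluation |
|---|---|---|
| IS/ES participants | 0, 3, 6 months | 0, 3, 6 months |
| IS/ES decliners | 6 months, if N is meant to include them (legend: practices only) | one contact, 6 months |
| MS participants | no code | one contact, 6 months |
| MS non-participants | 6 months, if coded N | one contact, 6 months |

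The EQ-5D row of the same table carries A and N at six months, so the CostQ row may simply have the wrong letter.

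**3. Recall.** None is stated. Three months is the natural reading: with six-month recall, the 3- and 6-month forms in IS/ES would count months 0-3 twice.

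**4. Formulae.** Let q be the share of patients on the full schedule, f the part of the six months that a single form covers, and s the share of total cost that comes only from the CostQ. Assume equal true values in all strategies and both quarters, and no filling-in of missing months.

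- Captured share of CostQ items = q + (1 − q) × f
- MS has q = 0, so its captured share is f.
- Gap in CostQ items = q × (1 − f)
- Gap in total cost = s × q × (1 − f)

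**5. Results with q = 0.30 in IS/ES (assumed).**

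| f | MS | IS/ES | Gap, CostQ items | Gap, total cost, s = 0.5 | s = 0.25 |
|---|---|---|---|---|---|
| 0.5 (three-month recall) | 50% | 0.30 + 0.70 × 0.5 = 65% | 15 points | 7.5% | 3.8% |
| 0.75 | 75% | 0.30 + 0.70 × 0.75 = 82.5% | 7.5 points | 3.8% | 1.9% |
| 1 (six-month recall) | 100% | 100% | 0 | 0 | 0 |

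Limited activity days come only from the CostQ, so the column for CostQ items applies to them in full.

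**6. Range for q.** If 60% of IS/ES patients were on the full schedule (assumed) and f = 0.5, IS/ES would capture 0.60 + 0.40 × 0.5 = 80%, and the gap would be 30 points.

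**7. Table 4 taken literally.** Suppose MS participants, 5% for illustration, get no form and the absent form counts as zero. MS then captures 0.95 × 0.5 = 47.5% at f = 0.5, and 95% at f = 1. Setting the recall period alone therefore does not close the gap; the codes must also be corrected.

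**The case against.** **The recall period is unknown.** The word quarterly may describe only how often IS and ES patients get the form, and an endpoint form with six-month recall is compatible with the text. This stands: the bias is conditional, and it vanishes at f = 1.

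**Other sources exist.** A reader might infer that half of all costs of non-participants are lost. The article does not support that. Prescribed medication comes from patient records (with permission) and practice contacts are registered. Only items that depend on the CostQ are exposed.

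**The problem is not confined to non-participants.** A reader of Table 4 alone might place it there. The Endpoint evaluation section puts every MS patient on the single contact, so the imbalance is mainly between MS and the other two strategies.

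**The 30% is not an enrolment rate.** In the sample size section it stands for frequent use of the program, whereas the schedule follows willingness to take part. This stands, and the 30% serves only as an illustration.

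**Imputation or scaling may be described elsewhere.** An article can leave that to the full plan, and nothing shown says that partial totals will be added to full ones unadjusted. But the collection schedule is fixed here. Months that were never asked about can be modelled at analysis, not recovered.

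**The light MS schedule is deliberate.** The Discussion says that research activity in MS is kept low because it could itself stimulate uptake. This is a sound reason not to add a three-month form there. It does not prevent the single form from covering the whole horizon.

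**Conclusion.** The point holds in conditional form. The article fixes a CostQ schedule that differs by strategy and participation, leaves MS participants uncoded, and states no recall period for a six-month comparison that is to include non-participants. With three-month recall and no filling-in, half of the questionnaire-only items are missing for every patient measured once.

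On the illustrative 30%, with equal true values and even accrual over the two quarters, the artificial gap is 15 points for limited activity days. For total cost it is 7.5% or 3.8% if half or a quarter of cost depends on the CostQ; those shares are assumptions. The direction favours MS. The gap is zero if everyone measured once, MS participants included, receives a form covering six months. The two participation-related primary and clinical questions are untouched; the economic objective is at risk.

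**What to change.** 1. **Reconcile Table 4** with Study design, Endpoint evaluation and Discussion. Code MS participants for the CostQ at six months, and make clear that N includes non-participating patients as well as practices.
2. **State the recall period.** For everyone measured only once, specify that the endpoint form covers the full six months. Ask about the two quarters separately, so that item 3 can be computed.
3. **Add a sensitivity analysis** of questionnaire-based costs and limited activity days restricted to months 3-6 in all strategies. It also serves patients who have already completed a form with shorter recall.

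The cost is small: corrected table codes, a change of wording in an online form, and a sentence or two in the economic analysis. Recruitment is described as ongoing, so the form can still be changed for patients who have not reached their endpoint. The drawback is that six-month recall is somewhat less accurate than two three-month recalls. An additional three-month form for patients measured once is not recommended, because it would work against the stated aim of limiting research activity in MS.

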## Discussion

This study is designed to investigate the effectiveness and cost effectiveness of implementing IBSM by comparing three different implementation strategies (MS, IS, and ES) in a three-arm cluster-randomized trial with a cluster pre-randomization design. The IBSM application contains functionalities that are characterized by some innovative aspects, such as options for e-consultation and integration of results into the general practice system. These functionalities address previously stated requirements for both patients and professionals. The findings of this study will lead to recommendations for a potential cost-effective strategy that can be used for the implementation of IBSM in practice.

This study has been designed for translation of research findings into actual practice. Primarily, the pre-cluster randomization design allows us to study the effect of the different implementation strategies on the number of primary care practices that participate in IBSM. Second, the impact of the different strategies at both professional and patient level on actual implementation (*i.e.*, participation, patient outcomes, and cost-effectiveness). Third, general practices are given a leading role to adapt and internalize IBSM in clinical practice: the project team will only act as facilitators to these practices. Additionally, the influence of research activities on implementation has been incorporated in the design of this study, because these might function as an extra stimulus for both practices and patients to adapt and internalize IBSM during the study period. Therefore, the content of the MS strategy is not only similar to commonly used (non-tailored) implementation strategies, but also the number and amount of research activities are minimized. This is in contrast to the IS and ES strategies, which are specifically designed to address previous identified barriers. These differences give us the opportunity to study how much support is required by general practices for IBSM implementation. Finally, this study evaluates the costs of the implementation from a societal perspective, which is in contrast to other implementation studies
[18,48]. Therefore, we will include costs for asthma care from both non-participating practices and non-participating patients.

### Implications

The results of this study will help to determine the most effective way of implementing IBSM. Both the pre-cluster randomization and the inclusion of the IS and ES strategies provide a more detailed view of the implementation process and thereby direction to the focus for future implementation processes in primary care. For example, it may provide information on: the quality and intensity of support professionals need to identify eligible patients; whether it is sufficient to focus only on the start-up period of implementation; and whether continuing support of professionals has additional value in maintaining implementation.

The results of this study can enhance a broad implementation of IBSM in current clinical care, based on a cost-effective strategy. Thereby it can contribute to improved care for patients with asthma. Furthermore, design and results of this trial can contribute to development of effective implementation strategies for self-management initiatives for other chronic diseases.

### Ethical approval

This study has been approved by the Medical Ethics Committee of the Leiden University Medical Centre.
